## Abstract

**Background:**

Uncomplicated chronic rachialgia is a highly prevalent complaint, and one for which therapeutic results are contradictory. The aim of the present study is to evaluate the effectiveness and safety of treatment with auriculopressure, in the primary healthcare sector, carried out by trained healthcare professionals via a 30-hour course.

**Methods/Design:**

The design consists of a multi-centre randomized controlled trial, with placebo, with two parallel groups, and including an economic evaluation. Patients with chronic uncomplicated rachialgia, whose GP is considering referral for auriculopressure sensory stimulation, are eligible for inclusion. Sampling will be by consecutive selection, and randomised allocation to one of the two study arms will be determined using a centralised method, following a 1:1 plan (true auriculopressure; placebo auriculopressure). The implants (true and placebo) will be replaced once weekly, and the treatment will have a duration of 8 weeks. The primary outcome measure will be the change in pain intensity, measured on a visual analogue scale (VAS) of 100 mm, at 9 weeks after beginning the treatment. A follow up study will be performed at 6 months after beginning treatment. An assessment will also be made of the changes measured in the Spanish version of the McGill Pain Questionnaire, of the changes in the Lattinen test, and of the changes in quality of life (SF-12). Also planned is an analysis of cost-effectiveness and also, if necessary, a cost-benefit analysis.

**Discussion:**

This study will contribute to developing evidence on the use of auriculotherapy using Semen vaccariae [wang bu liu xing] for the treatment of uncomplicated chronic rachialgia.

**Trial registration:**

Current Controlled Trials ISRCTN01897462.

## Background

Uncomplicated chronic rachialgia (UCR) is characterised by pain in the vertebral and paravertebral areas, the intensity of which varies depending on postures, movements and effort. It is usually associated with a painful limitation of mobility of the spine and sometimes with extensive or irradiated pain. The diagnosis of such complaints excludes fractures, direct traumas and systemic disease, but includes structural alterations of the spine, such as disc hernias or facetary alterations [1]. However, only 5% of the mechanical disorders of the spinal column that are treated in primary healthcare result from a structural alteration of the spine. The remaining 95% are comprised of non-specific neck and back pains [2]. Of all these locations, the lumbar region is most prevalent; between 60 and 70% of adults are estimated to have suffered this complaint at some time. Moreover, it tends to be persistent or recurrent [3] and in 95% of cases it is of non-specific muscular-skeletal origin [4]. In Spain, work time lost due to back pain is an average of 22 days per year, with an average cost of 1,260 euros per worker; the complaint represents 19–25% of the total expenditure on benefits for temporary sickness pay, and the total effect of back pain on the workplace has been estimated at an average of 55,388 days lost every year [5]. 90% of the patients with non-specific back pain return to work within six week [6]. Neck pain, on the other hand, is a problem that has been estimated to effect, at some time in life, 30% of men and 43% of women [7], becoming chronic among 10% of men and 17% of women. It is currently the second most important rheumatic cause for occupational invalidity [8]. Although the aetiology of neck pain is varied, ranging from tumoral problems to traumatisms, infections, inflammatory diseases and congenital diseases, in most cases no systemic causes can be identified, and so the largest such group is labelled as "non-specific neck pain". A recent study carried out in Finland estimated the annual prevalence of back pain to be 17% [9].

The treatment for non-specific back pain is usually conservative, and the standard procedure is to recommend pharmacological treatment with analgesic medication such as non-opiate analgesics, non steroidal anti-inflammatory drugs (NSAIDs), myorelaxants and opiates. The evidence derived from 51 studies examined in a systematic review [10] suggests that NSAIDs are effective for short-term symptomatic relief for patients with back pain, but there does not seem to be a specific variety of NSAID that is clearly more effective than any other. Myorelaxants are effective in treating non-specific back pain, but their adverse side effects mean they must be used with caution. Trials are needed to determine whether myorelaxants are more effective than analgesics or NSAIDs [11]. Multidisciplinary biopyschosocial rehabilitation for sub-acute pain in adults of working age has been analysed in a systematic review [12], which concluded that there exists a moderate degree of proof of the positive effectiveness of multidisciplinary rehabilitation. As this evidence is based on studies that presented some kind of methodological defect, and as various types of expensive multidisciplinary rehabilitation are commonly employed, there is an obvious need for high-quality trials to be carried out in this field [13].

Acupuncture and related techniques such as auriculotherapy have been used as therapeutic methods in China for over 2000 years, and are gaining increasing acceptance in the West, where their use has increased considerably in recent decades, especially for pathologies characterised by the presence of pain [14]. Stimulation of the auricular pavilion is usually employed as a technique associated with somatic acupuncture for alleviating pain, and also for sleep disorders, anxiety [15,16] or complaints of the autonomic nervous system [17], but it may also be used alone for the treatment of diverse muscular-skeletal pathologies [18-23], probably taking effect by means of an endorphinergic mechanism [24]. A wide variety of mappings have been made of the auricular pavilion, based on a supposed interconnection between the ear and the rest of the body, such that muscular-skeletal structures would be reflected, somatotopically, in the auricular pavilion [25,26]. Thus, any complaint of the muscles or skeleton would have an accurate representation within the ear, made evident as an increase in sensitivity to pressure or as a decrease in the electrical resistance of the skin [27]. The treatment usually consists of locating the sensitive points and then stimulating them with needles, which may be left in place for several days, or by the implantation of vaccaria seeds (*wang bu liu xing*), held within the auricular pavilion by means of small pieces of surgical tape. Nevertheless, as yet no clear relation has been determined between the somatic locations where muscular-skeletal pain is felt and the sensitive points within the auricular pavilion [28].

We have designed this randomised controlled multicentre study to investigate the effectiveness and safety of sensory stimulation via auricular implants in patients with UCR, treated by healthcare professionals (15 doctors and nurses) at 10 healthcare clinics in the Sevilla-Sur Healthcare District (within the Andalusian Public Health System). The primary specific goal is to assess effectiveness in terms of the lessened pain intensity, measured on a visual analogue scale (VAS), experienced by patients with UCR, at 9 weeks after beginning treatment. As secondary specific goals, we intend to: a) evaluate the effectiveness in terms of lessened pain intensity, measured on the VAS, at 6 months after beginning treatment; b) evaluate the effectiveness in terms of improvement recorded on the Spanish version of the McGill Pain Questionnaire (MPQ-SV), at 9 weeks and at 6 months after beginning treatment; c) evaluate the effectiveness in terms of patient-perceived improvement (PPI) at the end of the treatment; d) evaluate the impact on time lost off work due to sickness; e) evaluate the credibility of the technique and patients' expectations, as well as its relation to the results; f) evaluate the effectiveness in terms of reduced consumption of analgesic and anti-inflammatory medication; g) evaluate the effectiveness in terms of improved health-related quality of life (SF-12); h) compare the effectiveness of the technique with regard to the healthcare professionals' degree of training and practice; i) compare the characteristics of the Lattinen test and the MPQ-SV; j) analyze the cost-effectiveness of treatment with auricular pressure for patients with UCR.

This study is funded by the *Instituto de Salud Carlos III*, *Fondo de Investigaciones Sanitarias *(File No. PI0790058) and by the Health Ministry of the Andalusian Regional Government (File No. 00462007).

## Methods

### Design

Randomized controlled multicentre prospective study, with two parallel arms, to compare real auriculotherapy using vaccaria seeds (in accordance with traditional methods and with individual diagnoses) and placebo auriculotherapy. The patients will be blinded to both treatment methods. Analysis of the results will be carried out by professionals who will be blinded with respect to the allocation of patients to the different treatment groups.

### Duration of Study

May 2008–December 2009

### Subjects

Patients, recruited by the 15 doctors and nurses participating in the study at 10 Primary Healthcare Centers belonging to the Andalusian Public Health System (Sevilla-Sur Healthcare District), with symptoms of uncomplicated chronic rachialgia.

The patients included will be aged at least 18 years, with chronic uncomplicated muscular-skeletal rachialgia (neck, mid-back or lower back), diagnosed by clinical background and physical examination, and who have not previously received treatment with auricular implants. Exclusion criteria will include the protrusion or prolapse of one or more intervertebral discs with concurrent neurological symptoms; infectious spondylopathy; previous surgery of the spinal column; rachialgia caused by inflammatory disease, malign or autoimmmune; congenital deformities of the spinal column, except mild degrees of scoliosis or lordosis; vertebral fractures; spinal stenosis; spondylolysis or spondylolystesis; skin complaints in the auricular pavilion or allergy to sticking plaster; pregnancy; lawsuits brought by reason of rachialgia; incapacity to fill in the questionnaires or respond to the evaluator's questions.

The ethical validity of this study has been analyzed and approved by the Andalusian Government Committee for Clinical Trials, following the approval of the corresponding Research Commission at each of the participating Clinics. The study design takes into account the fundamental principles set out in the Helsinki Declaration, and those of the Council of Europe Convention concerning human rights and biomedicine, as well as the requirements under Spanish law in the field of biomedical research, the protection of personal data, and bioethics. All the patients involved must sign their informed consent to the proposed clinical research procedures. During the course of the study, audits will be performed as required by the relevant Research and Ethics Committee, as well as those of each Clinic's Quality Committee, independently of any external audits (such as that of the research financing body) that may be necessary.

### Randomization and treatment allocation

Sampling will be by consecutive selection in accordance with the inclusion-exclusion criteria, for a period of 12 months until the sample is complete. The randomized allocation to each of the two branches of the study will be carried out using specialized computer software (Epidat v. 3.1), at the Research Unit of the Costa del Sol Hospital (Málaga, Spain), in a 1:1 plan (true auricular pressure: placebo) in blocks of 6, stratified by therapist. Neither the clinics nor the healthcare professional participating in the study will be involved in the randomization process, and the randomization sequence will remain concealed until the end of the study. Patients who meet the criteria for inclusion and who sign their informed consent will be included in the study. After inclusion in the study, the healthcare professional will call the randomization clinic at which the patient is registered, and will be informed, both by phone and by fax, which of the two study branches the patient has been assigned to. This procedure ensures that the randomization process is not influenced by the healthcare personnel participating in the study. The success of the blinding of the patients will be evaluated at the end of the treatment period.

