### Treatment

The 15 healthcare professionals who will participate in the study (doctors and nurses) have taken a training course in auricular pressure techniques for the treatment of UCR, with a total of 15 hours' theory and 15 hours' practical content. Of these 15 professionals, 5 had also received specific training in acupuncture and related techniques, with an average of 320 hours theoretical training and over 100 hours' clinical practice with these techniques. All the patients will be allowed to use symptomatic medication for pain relief in case of need.

The patients in both groups will be called 8 times for treatment (once a week) for the auricular implants to be inserted.

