#### B) Placebo auriculotherapy (PAP)

The same protocol will be followed, under the same conditions as for TAP, but with the application of sticking plaster over inactive black plastic discs, with a diameter of 1.5 mm, simulating the appearance of the auricular implants used in the TAP.

Any adverse reactions or side effects that may occur will be recorded in the corresponding data logbook, stating details of the reaction, and date of occurrence.

The same time should be dedicated to the patients in each of the groups, as should that employed in the pre and post-session evaluations (Fig. 1).

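### One fixed block size of 6 within each therapist, who also recruits, treats and learns every allocation, leaves the choice of whom to enrol and when open to prediction; the claim that staff cannot influence the process is too broad

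*Protocol article*

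**What the plan says.** The section Randomization and treatment allocation describes a computer-generated list held at a central research unit, "in a 1:1 plan (true auricular pressure: placebo) in blocks of 6, stratified by therapist". Professionals take no part in generating it, and the sequence stays concealed to the end of the study. Sampling is consecutive. Once a patient has consented and been included, the professional calls the centre and "will be informed, both by phone and by fax, which of the two study branches the patient has been assigned to". The section then concludes: "This procedure ensures that the randomization process is not influenced by the healthcare personnel participating in the study".

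The Subjects section gives recruitment to the people who deliver treatment: "Patients, recruited by the 15 doctors and nurses participating in the study at 10 Primary Healthcare Centers". The Treatment section confirms that these are the trained operators: "The 15 healthcare professionals who will participate in the study (doctors and nurses) have taken a training course in auricular pressure techniques". They handle visibly different materials, vaccaria seeds in the true arm and, in the placebo arm, plaster "with the application of sticking plaster over inactive black plastic discs, with a diameter of 1.5 mm". On blinding, the Design section states "The patients will be blinded to both treatment methods" and adds that the analysts are blinded. It does not list the therapists as blinded.

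No varying block size is given, and nothing says that the block size is withheld from therapists.

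**The concern.** Each therapist works through a private sequence of 3:3 blocks and sees it revealed one patient at a time. Calling a central office hides the list but not its structure. Once three patients in a block have gone to one arm, the rest of that block is fixed. Even earlier in the block, the arm that lags is the more likely next assignment.

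The person with this information also decides whom to approach and when. A therapist with a belief about the method could, with or without intent, bring forward, postpone or discourage a patient according to the arm expected next. The arms would then differ in prognosis at entry, and that difference would pass into the primary comparison of VAS change at 9 weeks. Because the therapists cannot be blinded to materials they apply themselves, concealment of the next allocation is the main safeguard against this.

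**Working it through.** **Inputs.** Ratio 1:1, block size 6, stratum = therapist (Randomization and treatment allocation). 15 therapists (Subjects). 400 patients; mean reductions 32.3 and 19.8 mm; SD 31.9 mm; power 90%; α 5%, taken as two-sided (Sample size).

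**The plan's own figure.** Planned difference = 32.3 − 19.8 = 12.5 mm. n per group = 2 × (1.960 + 1.282)² × 31.9² / 12.5² ≈ 137, against 140 stated. 280 / 0.70 = 400, as stated. These figures are not in dispute. They are used only for scale: 400 / 15 ≈ 26.7 patients per therapist, assuming equal recruitment.

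**Predictability of one block.** A block of 6 with three of each arm has 20 equally likely sequences. For an observer who knows the block size and all earlier allocations in the stratum, full enumeration gives:

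| Position | 1 | 2 | 3 | 4 | 5 | 6 | Sum |
|---|---|---|---|---|---|---|---|
| Probability that the allocation is certain | 0 | 0 | 0 | 0.1 | 0.4 | 1 | 1.5 |
| Probability that the best guess is right | 0.5 | 0.6 | 0.6 | 0.7 | 0.7 | 1 | 4.1 |

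- Certain in advance: 1.5 / 6 = 25%.
- Guessed correctly: 4.1 / 6 = 68.3%.

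**Over 27 patients per therapist** (four full blocks and three patients of a fifth):

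- Certain: 4 × 1.5 / 27 = 22.2%.
- Guessed correctly: (4 × 4.1 + 0.5 + 0.6 + 0.6) / 27 = 18.1 / 27 = 67.0%.
- Over the trial, between 15 × 6 = 90 and 400 × 0.25 = 100 allocations could be known in advance if every therapist tracked the blocks.

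**Possible bias.** Suppose a patient steered towards an expected true allocation has an expected VAS change ν mm above average, and one steered towards an expected placebo allocation ν mm below. Per block, correct minus wrong guesses = 4.1 − 1.9 = 2.2. With three patients per arm:

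- Steering whenever one arm lags: 2.2ν / 3 = 0.73ν.
- Steering only on certain allocations: 1.5ν / 3 = 0.5ν.

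The documents give no value for ν. Over an assumed range:

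| Assumed ν | Steering whenever one arm lags | Only on certain allocations |
|---|---|---|
| 2 mm | 1.5 mm (12% of 12.5) | 1.0 mm (8%) |
| 5 mm | 3.7 mm (29%) | 2.5 mm (20%) |

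Every entry assumes that all 15 therapists always steer, in the same direction, with suitable patients always available, and that nothing is adjusted for. If a third of them did so, 3.7 mm would become about 1.2 mm.

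**Effect of varying the block size.** Simulation of 27 patients per therapist, with an optimal observer who knows the set of sizes but not the current one:

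| Block sizes | Certain | Guessed correctly |
|---|---|---|
| 6 only | 22.2% | 67% |
| 4, 6, 8 | 2.4% | 67% |
| 6, 8, 10 | 1.8% | 65% |

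Varying the size removes nearly all certainty but little of the guessing, because the therapist still sees the running tally within the stratum.

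**The case against.** The case for the plan has real substance.

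- **Knowledge of the block size is not established.** No section says therapists are told it, and certainty needs it to be known or inferred. This stands as a condition on the 25%. It does not dispose of the point: the article prints the block size, nothing says it is withheld, and favouring the lagging arm needs only a therapist's own past allocations.
- **Consecutive selection is the stated rule against picking patients.** It helps if enforced. But diagnosis rests on clinical history and examination, and the approach to the patient and its timing remain with the therapist.
- **The call comes after consent and inclusion, from a central list.** This does stop staff altering the sequence or reversing an assignment. Read that narrowly, the sentence about staff influence is largely true.
- **Baseline adjustment.** The Statistical analysis section adjusts for baseline level, age, sex, and pain intensity and frequency. That would remove part of any bias acting through measured severity, but not through unmeasured prognosis such as expected response.
- **Referral.** The Abstract mentions a GP considering referral, which might separate referral from treatment in some cases. The Subjects section still gives recruitment to the 15 professionals.

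A reader might infer that allocations are in fact being predicted, or that a bias of 3.7 mm, 29% of the planned difference, is to be expected. The documents support neither. The first needs knowledge of the block size and a running tally by the therapist; the second is an unadjusted worst case with universal steering and an assumed ν.

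**Conclusion.** The point holds as a weakness of design and wording. A single block size of 6 in therapist-level strata, with unblinded therapists who recruit, treat and learn each allocation, leaves up to 25% of allocations knowable in advance (about 22% over 27 patients per therapist) and 67–68% guessable, provided the therapist knows or infers the block size. The claim of no staff influence is sound for the sequence and for assignments already made, but not for whom to enrol or when.

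The effect on the primary comparison cannot be estimated from the document. 0.73ν is an upper bound under universal steering, and 0.5ν applies if only certain allocations are used. This is a risk of selection bias, not evidence that it occurred, and no calculation in the plan is wrong because of it. It merits a cheap improvement; the document does not support treating the primary comparison as compromised.

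**What to change.** For patients not yet enrolled:

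1. Generate the remaining list within therapist with randomly varying block sizes, for example 6, 8 and 10.
2. Withhold the sizes from the sites.
3. Limit the sentence on staff influence to what the procedure achieves: staff cannot alter the sequence or change an assignment.
4. State as a limitation that better-than-chance guessing stays near 65%, because each therapist sees all earlier allocations in the stratum.

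The cost is one new list from the research unit and slightly looser balance within therapist. The benefit is a fall in certain allocations from about 22% to about 2%.

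Replacing therapist strata with lists shared across therapists, for example by training level, would cut guessing further but is not part of this fix. It gives up balance by therapist and sits badly with the Discussion's aim of equal proportions of the two arms at every clinic.

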### Sample size

In calculating the sample size, a power of 90% and an α value of 5% were assumed, to detect a mean change in pain intensity, measured on the 100 mm visual analogue scale, of 32.3 mm between the initial and final values among the experimental group, and a mean reduction of 19.8 mm among the control group (standard deviation 31.9 mm), on the basis of the results of a pilot experiment carried out beforehand at the Pain Treatment Unit at the Dos Hermanas Healthcare Clinic between April and December 2006. These assumptions require a sample size of 140 patients per group, in a design with two equal groups. We propose to recruit 400 patients in order to allow for a 30% drop out rate.

### Treatment

The 15 healthcare professionals who will participate in the study (doctors and nurses) have taken a training course in auricular pressure techniques for the treatment of UCR, with a total of 15 hours' theory and 15 hours' practical content. Of these 15 professionals, 5 had also received specific training in acupuncture and related techniques, with an average of 320 hours theoretical training and over 100 hours' clinical practice with these techniques. All the patients will be allowed to use symptomatic medication for pain relief in case of need.

The patients in both groups will be called 8 times for treatment (once a week) for the auricular implants to be inserted.

